## **High mortality amongst hospitalised patients with HIV-associated TB despite TB treatment: derivation and validation of a predictive tool**

### **Statistical Analysis Plan**

#### **Introduction and background**

Despite the initiation of TB treatment and early ART, mortality in patients with HIV-associated TB (HIV-TB) who are admitted to hospital remains high.[1] A recent systematic review and meta-analysis found a 29% (95% CI 20-38%) mortality among hospitalised adults with HIV-TB.[2] Predictors of mortality vary between studies, but include current CD4 cell count, anaemia, indices of malnutrition and, as recently shown in a systematic review, urinary LAM-detection.[3–14]

Clinical predictor and prognostic scores have been developed and validated for HIV-positive patients presenting with PCP,[15] Cryptococcal meningitis [16] and pneumonia.[17] The TBScore was developed to predict outcome in pulmonary TB,[18] and a score to predict MTB bacteraemia amongst HIV-positive hospital admissions has also been developed.[19] No tool to predict mortality in HIV-TB patients admitted to hospital in sub-Saharan Africa (SSA) has been developed.

Furthermore, the aforementioned prediction tools have not been externally validated in different populations or settings, or had their impact evaluated.

A prognostic scoring tool for mortality in HIV-TB could be used in clinical practice to enhance the clinical care of patients with the worst prognosis. It could also have research applications, including aiding the development and evaluation of adjunctive interventions for HIV-TB, and identifying those patients who may benefit from such interventions.

#### **Aim**

To develop and validate a pragmatic, clinically applicable tool for use at admission for predicting early mortality (defined as < 2 months) in patients with HIV-TB admitted to hospital in SSA.

#### **Study population**

The population for developing the tool will be patients who are HIV-positive who are admitted to hospital and diagnosed with microbiologically/laboratory confirmed TB, defined as any positive:

- Mycobacterial culture

- Xpert MTB/RIF assay
- Determine TB-LAM assay

### **Outcome**

The outcome for this study will be early mortality, defined as death within 2 months of admission.

### **Methods: developing the prognostic model**

A cohort of patients with microbiologically confirmed HIV-TB admitted to hospital in high-prevalence settings in sub-Saharan Africa nested within the STAMP clinical [ref] trial will be used to develop the prognostic model.

- Clinically relevant and pragmatic demographic and clinical variables will be chosen for possible inclusion in the model based upon (1) a priori knowledge from existing studies, (2) based on univariate associations with mortality in development dataset (3) the need for unambiguous, reproducible variables that are available in most clinical settings where the tool may be used.
- In keeping with good practice, a minimum of 10 events (deaths) will be required for each candidate predictor studied.[25]
- Continuous variables (such as CD4 cell count and haemoglobin) will be kept as continuous predictors when practical or converted to ordered categorical variables or dichotomised to simplify the score (based on previously established cut-offs or data-derived categories based on associations with outcomes). Continuous variables will be assessed for non-linearity using fractional polynomials functions, and may need to be transformed in the regression models.
- Univariate associations between demographic and clinical variables and mortality will be tested using  $\chi^2$  and risk ratios with 95% CIs and/or logistic regression.
- A backward elimination stepwise approach to logistic regression modelling will be used to identify candidate predictor variables. Variables will be kept in the model based on p-values using likelihood ratio tests and Akaike information criterion (AIC), aiming to avoid overfitting.
- Further evaluation will include testing for interaction and comparing transformations of predictors where appropriate
- A clinical predictor score will be developed by giving dichotomous variables a value of 0 or 1, and using the regression coefficients from the logistic regression model to calculate the relative contribution of the variable to the risk score. Regression co-efficients will be

rounded to integers and/or scaled and assigned as points to each variable in the final risk score

- The score will be a continuous factor and an ordered categorical factor for simplification, with risk score categories being created based on plotting risk score against observed mortality.
- Missing data will be assumed to be missing at random. Complete case analysis will be used if observations missing data are <5%, otherwise multivariable multiple imputation with chained equations will be used to deal with missing data.

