**Appendix 1: Candidate variables for development dataset**

| Category                   | Variable                        | Comment                             |
|-----------------------------------|----------------------------------------|--------------------------------------------|
| Demographics               | Age                                    |                                            |
|                                   | Gender                                 |                                            |
|                                   | Date of admission                      |                                            |
|                                   | Site/study                             |                                            |
| HIV                        | New diagnosis                          | Yes/No                                     |
|                                   | ART status                             | Never/Currently
On/Interrupted etc..    |
|                                   | Time on ART/Date ART started           |                                            |
| TB                         | Previous history of TB                 | Yes/No                                     |
|                                   | Clinically suggested TB                | Yes/No                                     |
|                                   | Date of starting TB treatment          |                                            |
|                                   | Reason for starting TB treatment       |                                            |
| Admission                  | Reason for admission                   |                                            |
|                                   | Duration of illness                    |                                            |
|                                   | Presence of TB symptoms                | Cough, fever, night sweats,
weight loss |
|                                   | WHO TB symptom screen                  |                                            |
|                                   | Respiratory rate                       |                                            |
|                                   | Heart rate                             |                                            |

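### Candidates may be chosen by their association with death in the model-fitting data, and the SAP does not fix which set of variables its 10-deaths rule counts

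*SAP*

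**What the plan says.** All but two of the relevant statements are in the SAP section Methods: developing the prognostic model.

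- The first bullet says that "variables will be chosen for possible inclusion in the model based upon" three considerations: prior knowledge, univariable association in the development data ("based on univariate associations with mortality in development dataset"), and practicality. It gives no screening threshold and does not say whether all three must be satisfied.
- The second bullet sets the safeguard: "a minimum of 10 events (deaths) will be required for each candidate predictor studied". No number of candidates or expected deaths accompanies it.
- A later bullet uses the same word for what comes out of modelling: "A backward elimination stepwise approach to logistic regression modelling will be used to identify candidate predictor variables". Retention rests on likelihood ratio p-values and AIC, with no p-value cut-off.
- Continuous variables may be cut into "data-derived categories based on associations with outcomes". Fractional polynomials and interaction tests are also planned.
- Appendix 1 is titled "Candidate variables for development dataset" and lists everything before any screening.
- Methods: validating the prognostic model plans 100 bootstrap samples and external validation in other hospital cohorts. It does not say that screening and elimination are repeated in each bootstrap sample.

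**The concern.** When the deaths that fit the model also decide which variables are offered to it, every variable tried uses information, including those discarded. A limit on events per variable restrains overfitting only if its denominator includes all that was tried. Here the denominator is open, and on two of its three possible meanings the rule is counted after the outcome data have already shortened the list.

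The score's points are built from the fitted coefficients. A variable that passed by chance, or whose coefficient was selected because it happened to be large, would go directly into the bedside tool. The report could still state truthfully that the 10-deaths rule was met.

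**Working it through.** **The plan's own figure.** The figure of 10 is a rule, not a derived quantity, so there is nothing to reproduce. The check is what it implies under different denominators.

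**Meanings of *candidate*.** (a) The whole Appendix 1 list; (b) the variables chosen for possible inclusion, after univariable association has been used; (c) the output of backward elimination. Only (a) makes the rule count everything examined.

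**Size under (a), by row.** Non-outcome rows in Appendix 1: demographics 4 + HIV 3 + TB 4 + admission 11 + laboratory 3 + TB diagnostics 7 = 32.

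Deaths needed = 10 × 32 = 320. Patients = deaths / mortality, using the background "29% (95% CI 20-38%) mortality among hospitalised adults with HIV-TB", which is not a design assumption:

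- 320 / 0.29 = 1,103.4, so 1,104
- 320 / 0.38 = 842.1, so 843
- 320 / 0.20 = 1,600

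Dropping four rows as poor admission predictors (illustrative: dates, site/study and similar) gives 28 rows, 280 deaths and 280 / 0.29 = 965.5, so 966 patients. Merging overlapping rows (TB symptoms with the WHO symptom screen, urine LAM with LAM grade) lowers this further. In the other direction, ART status and reason for admission have several levels, one row bundles four symptoms ("Cough, fever, night sweats" and weight loss), and polynomial terms and interactions add parameters.

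**Chance passes at screening.** For 32 independent null variables, the expected number passing is 32 × 0.05 = 1.6 at p<0.05 and 32 × 0.20 = 6.4 at p<0.20. The chance that at least one passes at 0.05 is 1 − 0.95^32 = 0.806.

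**Noise variables kept.** Simulation with 400 patients, 29% mortality (400 × 0.29 = 116 deaths, or 116 / 32 = 3.6 per listed row) and 32 independent noise variables, all assumed:

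| Screen | Elimination | Mean noise variables kept |
|---|---|---|
| p<0.05 | p<0.05 | 1.4–1.5 |
| p<0.05 | AIC | 1.6 |
| p<0.10 | p<0.05 | 1.8 |
| p<0.10 | AIC | 3.2–3.3 |
| p<0.20 | p<0.05 | 1.8 |
| p<0.20 | p<0.10 | 3.2 |
| p<0.20 | AIC | 4.9–5.0 |

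Counted on the variables surviving the screen, the rule was met in 97–100% of runs.

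**Performance with some real signal.** Assumed: 32 independent standard-normal variables, five true predictors with log-odds ratio 0.3, 29% mortality, AIC elimination, 200 replicates, performance in 20,000 new patients. The SAP gives no number of deaths, so three values are shown.

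| Deaths | Candidates | Deaths per candidate entering elimination | Rule met | C, apparent / new | Calibration slope |
|---|---|---|---|---|---|
| 80 | screen p<0.05 | 22.6 | 99% | 0.700 / 0.612 | 0.54 |
| 80 | screen p<0.20 | 9.1 | 28% | 0.732 / 0.615 | 0.46 |
| 80 | 8 prespecified | 10.1 | 57% | 0.692 / 0.642 | 0.72 |
| 150 | screen p<0.05 | 29.7 | 100% | 0.690 / 0.647 | 0.76 |
| 150 | screen p<0.20 | 15.4 | 96% | 0.711 / 0.639 | 0.63 |
| 150 | 8 prespecified | 18.8 | 100% | 0.685 / 0.666 | 0.89 |
| 320 | screen p<0.05 | 51.3 | 100% | 0.686 / 0.663 | 0.87 |
| 320 | screen p<0.20 | 32.6 | 100% | 0.693 / 0.659 | 0.81 |
| 320 | 8 prespecified | 40.1 | 100% | 0.682 / 0.667 | 0.92 |

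The prespecified eight contain all five true predictors, which favours that row. With no true predictor, 150 deaths and a screen at p<0.20, the rule was met in every run, yet apparent C was 0.615 against 0.500 in new patients.

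**What 10 per parameter buys.** Expected shrinkage S solves n = P / [(S − 1) ln(1 − R²/S)], with P parameters and R² on the Cox–Snell scale. Assume Nagelkerke R² 0.15. The Cox–Snell maximum at 29% mortality is 0.70, so R² = 0.15 × 0.70 = 0.105. With n/P = 10 / 0.29 = 34.5, S = 0.795. Coefficients would then be 1 / 0.795 = 1.26 times too large, about 26%.

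**The case against.** The strongest reply is textual. The rule is worded per candidate predictor *studied*, which can naturally mean every predictor examined, and the SAP nowhere says that it is counted after screening. A reader might infer that the plan counts only survivors and that its safeguard is void. The document does not support that: it is one permitted reading, and the literal one is strict. What stands is that nothing commits the analyst to the strict reading.

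Second, Appendix 1 also lists outcomes and dates, so it looks partly like a data-extraction list. Date of admission, site/study and the start of TB treatment fit poorly with a tool meant for use at admission, and the two outcome-free criteria could remove such rows at no statistical cost. This stands: 320 deaths is an upper reading by row, not the plan's requirement.

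Third, points come from relative contributions that are scaled and rounded, and risk categories from observed mortality, so uniform inflation of coefficients largely cancels in the score. This also stands. It does not cover noise variables or uneven inflation from selection, nor predicted probabilities taken from the model.

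Fourth, bootstrap and external validation are planned. They can reveal optimism but do not prevent it, and a bootstrap that omits the selection steps leaves the optimism due to selection uncorrected.

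Finally, defining the denominator and repeating selection within the bootstrap might be enough without dropping the univariable criterion. That would make the accounting honest and measure the optimism, but outcome-driven selection would continue.

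**Conclusion.** The point holds in a limited form. The SAP permits outcome-based choice of candidates in the fitting data and leaves the denominator of its 10-deaths rule unfixed, so the rule need not protect against overfitting from the wider list. It does not follow that the rule will be counted on survivors, or that it never bites: in the simulation with 80 deaths and a screen at p<0.20 it was met in only 28% of runs.

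The size depends on quantities that the SAP does not give. About 1.4 to 5 retained noise predictors assumes 400 patients and 32 independent noise variables, and varies with the thresholds. The calibration slopes of 0.46 to 0.87 after screening, against 0.72 to 0.92 with eight prespecified candidates, depend on the assumed deaths, effects and independence. Real candidates are correlated, and fewer than 32 are likely to be modelled. The change is worth making because it alters a stated method at little cost.

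**What to change.** 1. Remove univariable association as a selection criterion, and keep those results as description only.
2. Choose candidates by prior knowledge and practicality before looking at outcomes. Merge duplicate rows and drop those not usable at admission.
3. State that the 10-deaths rule applies to every parameter examined, including category levels, polynomial terms and interactions. Give the available deaths, and shorten the list if they fall short.
4. Repeat all data-driven selection steps in every bootstrap sample, and use the estimated optimism to shrink the coefficients. This is needed even when the rule is met, as the shrinkage figure at 10 deaths per parameter shows.

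The cost is SAP wording, fewer candidates, a little more analysis work and possibly a lower reported C-index. No extra patients are needed.

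### The SAP lets cut-offs for continuous predictors be chosen by their association with death, in the same data that then select variables, set points and give the C-index

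*SAP*

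**What the plan says.** All of the following is in the SAP, Methods: developing the prognostic model, unless stated otherwise.

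- **Form of predictors.** Continuous variables "will be kept as continuous predictors when practical or converted to ordered categorical variables or dichotomised to simplify the score". The basis for conversion is "based on previously established cut-offs or data-derived categories based on associations with outcomes". Nothing says which basis applies to which variable or how many cut-offs may be tried. The same bullet plans fractional polynomials to check non-linearity.
- **Retention.** "Variables will be kept in the model based on p-values using likelihood ratio tests and Akaike information criterion (AIC), aiming to avoid overfitting". No p-value threshold is given.
- **Points.** Dichotomous variables are coded 0 or 1, and points come from "using the regression coefficients from the logistic regression model to calculate the relative contribution of the variable to the risk score".
- **Sample size rule.** "a minimum of 10 events (deaths) will be required for each candidate predictor studied". It is not said whether each cut-off tried counts as a candidate.
- **Candidates.** Appendix 1 lists at least nine continuous measures (age, respiratory rate, heart rate, systolic blood pressure, temperature, weight/BMI, CD4 count, haemoglobin, C-reactive protein), with no cut-off for any of them.
- **Validation.** Methods: validating the prognostic model plans 100 bootstrap resamples and external validation in two other datasets. It treats a C-index below 0.6 as poor and lets the validation data be used to re-calibrate or revise the model.

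**The concern.** A cut-off picked because it separates deaths from survivors has already used the outcome. A likelihood ratio test or AIC comparison at that cut-off treats it as fixed and gives no penalty for the search. Three consequences follow: irrelevant predictors are retained too often, coefficients at the chosen cut are too large, and the C-index computed in the same patients is too high. Because points are scaled from the coefficients, the second error enters the bedside score directly. The SAP states that it wants to avoid overfitting, and this option works against that aim.

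**Working it through.** The SAP gives no sample size, retention threshold or expected C-index, so it has no figure of its own to reproduce. The size of the effect was found by simulation.

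**Inputs.**
- Mortality 29%, range 20-38%: the SAP's Introduction and background reports that a meta-analysis "found a 29% (95% CI 20-38%) mortality among hospitalised adults with HIV-TB". Using it as 2-month mortality is an assumption.
- Development sample size: assumed, 200 to 1000.
- Retention level: assumed two-sided 5%, critical value 1.96² = 3.84. AIC used alone is looser, since it keeps a one-parameter term once the likelihood ratio statistic exceeds 2.

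**Step 1: one predictor with no effect.** For each cut-off, with h(x) = x ln x, the 2×2 likelihood ratio statistic is 2[Σh(cells) − Σh(row totals) − Σh(column totals) + h(n)]. The cut-off with the largest value is kept and compared with 3.84 (5000 datasets per setting, 29% mortality).

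| Cut-offs searched | False positives, n=300 | False positives, n=500 | Median OR, n=300 |
|---|---|---|---|
| 1, fixed at the median | 4.9% | 5.3% | 1.19 |
| 2 (tertiles) | 8.5% | 9.7% | 1.31 |
| 3 (quartiles) | 12.7% | 13.8% | 1.38 |
| 9 (deciles) | 25.2% | 24.8% | 1.62 |
| all in the central 80% | 47.6% | 47.0% | 1.82 |

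Across n = 200-1000 at 29% mortality, and 20-38% mortality at n=300, the full search gives 44-48%. A separate run with the chi-square statistic (4000 datasets, n=500) gave 12.4% for quartiles, 25.0% for deciles and 44.7% for the full search.

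As a rough check, k independent tests would give 1 − 0.95^k: 9.8% for k=2, 14.3% for k=3 and 37.0% for k=9. Neighbouring cut-offs are correlated, so the simulated values should lie below these, and they do.

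**Step 2: a whole score.** The setting is n=300, baseline risk 29% and eight continuous candidates: three real (log-OR per SD 0.5, 0.4, 0.3) and five null. All are dichotomised, then backward elimination (Wald, 5%) is run and points equal the coefficients. Each of 300 scores was tested in 20,000 new patients. With 300 × 0.29 = 87 deaths, 87/8 = 10.9 per candidate, so the ten-event rule is met if each variable counts once.

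| | Outcome-chosen cuts | Fixed cuts (median) |
|---|---|---|
| Null predictors kept, of 5 | 2.12 | 0.25 |
| At least one null kept | 92% | 23% |
| Mean coefficient, fitted / new data | 1.08 / 0.40 | 0.79 / 0.58 |
| C-index, apparent / new data | 0.741 / 0.610 | 0.643 / 0.607 |

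Coefficients are overstated by 1.08/0.40 = 2.7 times against 0.79/0.58 = 1.4 times. The C-index is overstated by 0.741 − 0.610 = 0.131 against 0.643 − 0.607 = 0.036.

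**Step 3: does the bootstrap remove it?** In the first 100 of these datasets (100 resamples each), the apparent C-index was 0.743 and the true value 0.608, an excess of 0.135. With cut-offs held fixed, the correction reaches 0.708 and removes 0.035. With the search repeated in every resample it reaches 0.647 and removes 0.096.

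**The case against.** - **The search is optional and its timing is open.** Continuous form comes first, established cut-offs are named before data-derived ones, and conversion is meant to simplify the score. Fitting a continuous model and categorising afterwards is compatible with the text. This stands: a reader might infer that dichotomising must precede elimination and so throws away the fractional-polynomial work, but the SAP does not say so. Still, points taken from coefficients of 0/1 variables suggest that the cut-offs exist by the time that model is fitted.
- **45% is the worst case.** It needs an exhaustive search, which the SAP does not describe; tertiles or quartiles give about 9-14%. It also concerns a null predictor, whereas the SAP's introduction already names CD4 count and anaemia as predictors of death. For those two, the issue is exaggerated points rather than false selection. This stands, but the SAP sets no limit on the search and Appendix 1 holds many other continuous candidates.
- **Validation is planned.** External data can show the drop in performance. They do not repair the chosen variables or points, and once used to revise the model they no longer test it independently. It would go too far to say the cut-offs will fail in those cohorts, since their data are not in the document.
- **Fixed cut-offs do not sharpen the score.** In new patients the C-index was 0.610 against 0.607. This stands: the gain is honest reporting and sounder points. Nor does the example cross the SAP's 0.6 benchmark.
- **Risk groups.** A reader might extend the point to the score categories, "with risk score categories being created based on plotting risk score against observed mortality". Grouping a finished score involves no selection test and cannot change the points or the continuous score's C-index, so the argument does not carry over.

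**Conclusion.** The concern holds as a conditional one. The SAP expressly permits outcome-chosen cut-offs and reuses the same deaths for retention, points and C-index, with no stated correction. If the option is used before or during modelling, the false-positive rate for a null predictor rises from 5% to about 9% for a tertile search and about 45% for a full search of the central 80%. Points and the apparent C-index are inflated in the same direction. The false-positive rates change little over the sample sizes and mortality tried, but rest on the assumed 5% level. The score-level figures also depend on the assumed sample size, effect sizes and a full search on all eight candidates, so they illustrate the mechanism and do not forecast this study's result.

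**What to change.** 1. In the bullet on continuous variables, delete the second basis for categories, the one derived from the outcome.
2. State that variable selection and model fitting use continuous predictors in continuous form, linear or fractional polynomial.
3. Convert to points only afterwards, at established cut-offs listed with their source in Appendix 1 before outcomes are examined, or at outcome-blind quantiles where no established cut-off exists.
4. If any data-derived cut-off is kept, state that every bootstrap resample repeats both the cut-off search and the variable selection, and report the optimism-corrected C-index. This is second best: in the illustration it still gave 0.647 against a true 0.608.

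The cost is SAP wording only. Apparent performance in the development data will be lower, possibly noticeably: 0.741 to 0.643 in the illustration (median cuts), with performance in new patients essentially unchanged. Continuous modelling may do better: the full continuous model reached 0.664 in new patients. That comparison used truly linear effects, no elimination and no conversion to points, so part of the gain would be lost in the final score.
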